#### **10.1.3. Phase II trial: Cohort H (NSCLC)**

- We rely on a single-arm phase 2 trial based on an optimal two-stage Simon's design [91].
- Treatment will be considered promising if 6-month PFR ( $\geq 20\%$ ).
- Hypotheses are the following [62] :
  - 20% 6-month PFR (null hypothesis),
  - 40% acceptable 6-month PFR (alternative hypothesis),
  - 5% 1-sided type I error rate,
  - 80% power,
- A total of 43 eligible and assessable subjects will be necessary, with 13 assessable subjects recruited to the first stage.
- Stage 1: Following the inclusion of the first 13 assessable patients, if 3 or less patients are progression-free at 6 months (complete response, partial response or stable disease), the study will be terminated early. Otherwise, if 4 or more patients are progression-free at 6 months, the second group of subjects will be recruited.
- Stage 2: If at the end of recruitment, 13 patients or more are progression-free at 6 months (out of the 43 eligible and evaluable patients), treatment will be considered worthy of further testing in this disease (efficacy rate  $\geq 20\%$ ).
- Inclusions will not be suspended after the recruitment of the first 13 patients while data are being analysed for the first stage of inclusion.
- In order to account for not evaluable patients (+/- 10%), 47 patients will be recruited.

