#### **10.1.4. Phase II trial: Cohort I (Solid tumors-TLS+)**

- We rely on a single-arm phase 2 trial based on an optimal two-stage Simon's design [91].
- Treatment will be considered promising if 6-month PFR ( $\geq 15\%$ ).
- Hypotheses are the following:
  - 15% 6-month PFR (null hypothesis),
  - 40% acceptable 6-month PFR (alternative hypothesis),
  - 5% 1-sided type I error rate,
  - 90% power,
- A total of 29 eligible and assessable subjects will be necessary, with 13 assessable subjects recruited to the first stage.
- Stage 1: Following the inclusion of the first 13 assessable patients, if 2 or less patients are progression-free at 6 months (complete response, partial response or stable disease), the study will be terminated early. Otherwise, if 3 or more patients are progression-free at 6 months, the second group of subjects will be recruited.
- Stage 2: If at the end of recruitment, 8 patients or more are progression-free at 6 months (out of the 29 eligible and evaluable patients), treatment will be considered worthy of further testing in this disease (efficacy rate  $\geq 15\%$ ).
- Inclusions will not be suspended after the recruitment of the first 13 patients while data are being analysed for the first stage of inclusion.
- In order to account for not evaluable patients (+/- 10%), 32 patients will be recruited.

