#### **10.1.5. Phase II trial: Cohort A' (Colorectal @ 80 mg), with immune signature (based on low tumor-associated macrophages infiltrate level)**

- We rely on a single-arm phase 2 trial based on an optimal two-stage Simon's design [91].
- Treatment will be considered promising if 4-month PFR  $\geq 20\%$ .
- Hypotheses are the following:
  - 20% 4-month PFR (null hypothesis),
  - 40% acceptable 4-month PFR (alternative hypothesis),
  - 5% 1-sided type I error rate,
  - 80% power,
- A total of 43 eligible and assessable subjects will be necessary, with 13 assessable subjects recruited to the first stage.

- Stage 1: Following the inclusion of the first 13 assessable patients, if 3 or less patients are progression-free at 4 months (complete response, partial response or stable disease), the study will be terminated early. Otherwise, if 4 or more patients are progression-free at 4 months, the second group of subjects will be recruited.
- Stage 2: If at the end of recruitment, 13 patients or more are progression-free at 4 months (out of the 43 eligible and evaluable patients), treatment will be considered worthy of further testing in this disease (efficacy rate  $\geq 20\%$ ).
- Inclusions will not be suspended after the recruitment of the first 13 patients while data are being analysed for the first stage of inclusion.
- In order to account for not evaluable patients (+/- 10%), 47 patients will be recruited.

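### In cohorts H, I and A' accrual continues while stage 1 matures, so the Simon optimal designs lose part of their expected saving; closing accrual once the stage 1 boundary is out of reach recovers some of it with no change in error rates

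*Protocol*

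**What the plan says.** Protocol sections 10.1.3 (cohort H), 10.1.4 (cohort I) and 10.1.5 (cohort A') each specify a Simon optimal two-stage design with a "5% 1-sided type I error rate".

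- **H:** 20% versus 40% progression-free at 6 months, 80% power. Stop if 3 or fewer of 13 are progression-free; success needs 13 or more of 43.
- **I:** 15% versus 40% at 6 months, 90% power. Stop if 2 or fewer of 13; success needs 8 or more of 29.
- **A':** rates, power and boundaries as in H, but with the endpoint at 4 months.

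The stage 1 bullet for H ends: "Otherwise, if 4 or more patients are progression-free at 6 months, the second group of subjects will be recruited". A later bullet in the same section says: "Inclusions will not be suspended after the recruitment of the first 13 patients while data are being analysed". Sections 10.1.4 and 10.1.5 carry the same pair of statements with their own boundary and time point.

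Section 8.2.2.1 has scans at weeks 8, 16 and 24 reviewed centrally, and section 9.2.1 calls this review in-stream. Section 10.1.2 lets cohorts A to G suspend inclusion when accrual is fast. Sections 10.1.3 to 10.1.5 contain no such exception and no expected accrual rate.

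**The concern.** Among two-stage designs meeting the same error constraints, the optimal design is the one with the smallest expected number of patients under the null. That expectation assumes that no one enters stage 2 until stage 1 has been read. Here the read comes months after the 13th patient, and accrual goes on meanwhile. Some of the patients whom the stop was meant to spare are enrolled before it can act.

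Part of that run-on is avoidable. The stage 1 result is often settled before the 13th patient's last scan: in H and A' it is fixed at the 10th failure among the 13, in I at the 11th. The protocol has no rule that closes accrual at that moment, so patients can still enter a cohort whose stage 1 result is already decided. The reader is also left with a stage 1 bullet that makes recruitment of the second group follow a pass, and a no-suspension bullet that lets it begin beforehand.

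**Working it through.** **1. Reproducing the designs.** Let X be the number progression-free among the first 13, so X ~ Bin(13, p).

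PET = P(X ≤ r1 | p0) and EN = 13 + (1 − PET) × (n − 13).

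- H and A' (3/13, 12/43; p0 = 0.20): PET = 0.747; EN = 13 + 0.253 × 30 = 20.6; alpha 0.0496; power 0.800.
- I (2/13, 7/29; p0 = 0.15): PET = 0.692; EN = 13 + 0.308 × 16 = 17.9; alpha 0.0500; power 0.907.

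The boundaries are correct. The EN values hold only if accrual pauses at 13.

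**2. Why curtailment changes no decision.** In H and A', X ≤ 3 is the same event as at least 13 − 3 = 10 failures. In I, X ≤ 2 is the same event as at least 13 − 2 = 11 failures. A trial that closes at the 10th (11th) failure is one that the written rule would have stopped, and the reverse also holds. Alpha, power and PET are therefore identical.

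**3. Enrolment when stage 1 fails under the null.** Assumptions:
- exponential PFS with S(T) = p0;
- Poisson accrual;
- failures seen at weeks 8, 16 and 24 (8 and 16 in A'), with no reporting delay;
- all enrolled patients assessable, capped at 43 (H), 29 (I) and 43 (A').

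The accrual rate is not stated, so it is varied. The lowest value is the protocol-wide average from the Synopsis: 735 patients / (72 months × 17 cohorts) = 0.60 per month.

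Mean enrolled at a stop, by simulation, as written versus curtailed:

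| Rate per month | H | I | A' |
|---|---|---|---|
| 0.6 | 16.3 vs 13.6 | 16.3 vs 13.9 | 15.2 vs 13.2 |
| 1 | 18.6 vs 15.0 | 18.5 vs 15.4 | 16.7 vs 14.2 |
| 2 | 24.1 vs 18.8 | 23.9 vs 19.3 | 20.4 vs 16.9 |
| 4 | 34.9 vs 27.4 | 28.8 vs 26.3 | 27.7 vs 22.8 |

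Hand check of the as-written column: enrolment is about 13 + rate × wait. In H, 24 weeks is 5.52 months, giving 13 + 2 × 5.52 = 24.0. In A', 16 weeks is 3.68 months, giving 13 + 2 × 3.68 = 20.4.

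**4. Effect on EN under the null**, as PET × (enrolled at a stop) + (1 − PET) × n:
- H at 0.6: 0.747 × 16.3 + 0.253 × 43 = 23.1, against 20.6.
- H at 2: 0.747 × 24.1 + 0.253 × 43 = 28.9.
- H at 4: 0.747 × 34.9 + 0.253 × 43 = 36.9.
- I at 2: 0.692 × 23.9 + 0.308 × 29 = 25.5, against 17.9.
- A' at 2: 0.747 × 20.4 + 0.253 × 43 = 26.1, against 20.6.

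**5. Share of stage 2 still spared as written, at 0.6, 1, 2 and 4 per month**, as (n − enrolled)/(n − 13):
- H: 89%, 81%, 63%, 27%.
- I: 79%, 66%, 32%, 1%.
- A': 93%, 88%, 75%, 51%.

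**6. Share of the lost saving that curtailment recovers in H**, as (as written − curtailed)/(as written − 13):
- 0.6: 2.7/3.3 = 82%.
- 1: 3.6/5.6 = 64%.
- 2: 5.3/11.1 = 48%.
- 4: 7.5/21.9 = 34%.

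The share falls with faster accrual because the deciding failure then comes later. At 4 per month in H it is a week 24 scan in 53% of stops and a week 8 scan in only 6%.

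**The case against.** The strongest reply is that running on is an open and legitimate choice. Pausing for 4 to 6 months costs time and momentum, and the protocol says plainly that it will not pause. The stage 1 bullet says that the second group is recruited if the boundary is passed, not only if it is passed, and the later bullet can be read as clarifying it. Nothing forbids an early stop: central review is in-stream, and the Steering Committee evaluates benefit and risk during the trial (section 12.1.1). All of this stands. It makes the point an improvement to a stated trade-off, not the correction of an error, and curtailment respects the choice because accrual stays open.

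Two stronger readings are tempting, and the documents support neither.

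- **That the stop spares few patients.** This needs about 4 to 5 patients per month in H, 2 to 3 in I and 7 in A'. The protocol gives no rate for these cohorts. At the 0.6 average the stop still spares about 89%, 79% and 93% of stage 2. That average assumes that all 17 cohorts are open for all 72 months, so the pace of an open cohort may be higher, but how much higher is not stated.
- **That curtailment repairs the loss wherever it occurs.** In H it recovers about half or more up to roughly 2 per month and only about a third at 4 per month, so it helps least where the run-on is largest.

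Run-on also does not inflate the type I error: the stage 1 boundary and final rule are unchanged.

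**Conclusion.** The point holds in a conditional form. The run-on rule means that the expected sample sizes behind the choice of an optimal design (20.6 in H and A', 17.9 in I) are not achieved. The excess is modest at the protocol-wide average pace and large at several patients per month. Closing accrual when the boundary becomes unreachable saves, on average per failed stage 1, 2.7 to 7.5 patients in H, 2.3 to 4.6 in I (2.5 at 4 per month, where the cap of 29 binds) and 2.0 to 4.9 in A' over the rates examined.

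That curtailment leaves the decision unchanged is exact. The patient counts rest on exponential PFS, Poisson accrual, no reporting delay and full assessability. A one-month analysis delay raises enrolment at the stop: in H at 2 per month the share of stage 2 spared falls from 63% to 57%. The A' figures take the 4-month endpoint of section 10.1.5 at face value. Section 9.2.1 defines its progression-free status partly by stable disease of more than 24 weeks; that needs reconciling and could lengthen the wait.

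**What to change.** In sections 10.1.3 to 10.1.5:

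1. Keep accrual open after the 13th patient, but close it as soon as 10 (H, A') or 11 (I) of the first 13 patients, each confirmed eligible and assessable under section 10.2.2, have failed the endpoint on central review.
2. Reword the stage 1 bullet so that it agrees with the no-suspension bullet: enrolment continues while stage 1 matures and goes on to the full sample size unless the stage 1 stop is met.
3. State that patients enrolled beyond 13 when a cohort stops are reported descriptively and do not reopen the stage 1 decision.

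The cost is a few sentences per section and a running count of failures from reviews already planned. The one real burden is confirming eligibility and assessability in real time for each counted failure, since section 10.2.2 replaces patients who are not assessable. Alpha, power, sample size and the stage 1 decision do not change.

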#### **10.1.4. Phase II trial: Cohort I (Solid tumors-TLS+)**

- We rely on a single-arm phase 2 trial based on an optimal two-stage Simon's design [91].
- Treatment will be considered promising if 6-month PFR ( $\geq 15\%$ ).
- Hypotheses are the following:
  - 15% 6-month PFR (null hypothesis),
  - 40% acceptable 6-month PFR (alternative hypothesis),
  - 5% 1-sided type I error rate,
  - 90% power,
- A total of 29 eligible and assessable subjects will be necessary, with 13 assessable subjects recruited to the first stage.
- Stage 1: Following the inclusion of the first 13 assessable patients, if 2 or less patients are progression-free at 6 months (complete response, partial response or stable disease), the study will be terminated early. Otherwise, if 3 or more patients are progression-free at 6 months, the second group of subjects will be recruited.
- Stage 2: If at the end of recruitment, 8 patients or more are progression-free at 6 months (out of the 29 eligible and evaluable patients), treatment will be considered worthy of further testing in this disease (efficacy rate  $\geq 15\%$ ).
- Inclusions will not be suspended after the recruitment of the first 13 patients while data are being analysed for the first stage of inclusion.
- In order to account for not evaluable patients (+/- 10%), 32 patients will be recruited.

#### **10.1.5. Phase II trial: Cohort A' (Colorectal @ 80 mg), with immune signature (based on low tumor-associated macrophages infiltrate level)**

- We rely on a single-arm phase 2 trial based on an optimal two-stage Simon's design [91].
- Treatment will be considered promising if 4-month PFR  $\geq 20\%$ .
- Hypotheses are the following:
  - 20% 4-month PFR (null hypothesis),
  - 40% acceptable 4-month PFR (alternative hypothesis),
  - 5% 1-sided type I error rate,
  - 80% power,
- A total of 43 eligible and assessable subjects will be necessary, with 13 assessable subjects recruited to the first stage.

- Stage 1: Following the inclusion of the first 13 assessable patients, if 3 or less patients are progression-free at 4 months (complete response, partial response or stable disease), the study will be terminated early. Otherwise, if 4 or more patients are progression-free at 4 months, the second group of subjects will be recruited.
- Stage 2: If at the end of recruitment, 13 patients or more are progression-free at 4 months (out of the 43 eligible and evaluable patients), treatment will be considered worthy of further testing in this disease (efficacy rate  $\geq 20\%$ ).
- Inclusions will not be suspended after the recruitment of the first 13 patients while data are being analysed for the first stage of inclusion.
- In order to account for not evaluable patients (+/- 10%), 47 patients will be recruited.

#### **10.1.6. Phase II trial : Cohorts J (Urothelial cancer) and L (Triple negative breast cancer)**

- We rely on a single-arm phase 2 trial based on an exact single stage design (A'Hern).
- Treatment will be considered promising if 6-month DCR  $\geq 15\%$ .
- Hypotheses are the following:
  - 15% 6-month DCR (null hypothesis),
  - 35% 6-month DCR (alternative hypothesis),
  - 5% 1-sided type I error rate,
  - 80% power,
- A total of 28 eligible and assessable subjects will be necessary. If at the end of recruitment, 8 patients or more have disease control at 6 months (out of the 28 eligible and evaluable patients), treatment will be considered worthy of further testing in this disease (efficacy rate  $\geq 15\%$ ).
- In order to account for not evaluable patients (+/- 10%), 31 patients will be recruited.

#### **10.1.7. Phase II trials: Cohort K (HPV-associated cancer)**

- We rely on a single-arm phase 2 trial based on an exact single stage design (A'Hern).
- Treatment will be considered promising if 6-month DCR  $\geq 10\%$ .
- Hypotheses are the following:
  - 10% 6-month DCR (null hypothesis),
  - 25% 6-month DCR (alternative hypothesis),
  - 5% 1-sided type I error rate,
  - 80% power,
- A total of 40 eligible and assessable subjects will be necessary. If at the end of recruitment, 8 patients or more have disease control at 6 months (out of the 40 eligible and evaluable patients), treatment will be considered worthy of further testing in this disease (efficacy rate  $\geq 10\%$ ).
- In order to account for not evaluable patients (+/- 10%), 44 patients will be recruited.

#### **10.1.8. Phase II trials: Cohorts M (TMB-high solid tumors) and O (Non clear-cell renal carcinoma)**

- We rely on a single-arm phase 2 trial based on an exact single stage design (A'Hern).
- Treatment will be considered promising if 6-month PFR  $\geq 20\%$  (Cohort M: Marabelle A et al. Lancet Oncol. 2020 ; cohort O: David F McDermott et al. J Clin Oncol 2021).
- Hypotheses are the following:
  - 20% 6-month PFR (null hypothesis),
  - 40% 6-month PFR (alternative hypothesis),
  - 5% 1-sided type I error rate,
  - 80% power,
- A total of 35 eligible and assessable subjects will be necessary. If at the end of recruitment, 12 patients or more are progression-free at 6 months (out of the 35 eligible and evaluable patients), treatment will be considered worthy of further testing in this disease (efficacy rate  $\geq 20\%$ ).
- In order to account for not evaluable patients (+/- 10%), 39 patients will be recruited.

#### **10.1.9. Phase II trials: Cohort N (MSI-high solid tumors)**

- We rely on a single-arm phase 2 trial based on an exact single stage design (A'Hern).
- Treatment will be considered promising if 6-month PFR  $\geq 15\%$ .
- Hypotheses are the following:
  - 15% 6-month PFR (null hypothesis),
  - 35% 6-month PFR (alternative hypothesis),

- 5% 1-sided type I error rate,
  - 80% power,
- A total of 28 eligible and assessable subjects will be necessary. If at the end of recruitment, 8 patients or more are progression-free at 6 months (out of the 28 eligible and evaluable patients), treatment will be considered worthy of further testing in this disease (efficacy rate  $\geq 15\%$ ).
- In order to account for not evaluable patients (+/- 10%), 31 patients will be recruited.

#### **10.1.10. Phase II trials: Cohort P (Malignant pleural mesothelioma)**

- We rely on a single-arm phase 2 trial based on an exact single stage design (A'Hern).
- Treatment will be considered promising if 6-month PFR  $\geq 10\%$ .
- Hypotheses are the following:
  - 10% 6-month PFR (null hypothesis),
  - 25% 6-month PFR (alternative hypothesis),
  - 5% 1-sided type I error rate,
  - 80% power,
- A total of 40 eligible and assessable subjects will be necessary. If at the end of recruitment, 8 patients or more are progression-free at 6 months (out of the 40 eligible and evaluable patients), treatment will be considered worthy of further testing in this disease (efficacy rate  $\geq 10\%$ ).
- In order to account for not evaluable patients (+/- 10%), 44 patients will be recruited.

### **10.2. DEFINITION OF STUDY POPULATIONS**

#### **10.2.1. Phase I (Dose escalation part)**

The following patients will be included in the population assessable for safety (primary analysis):

- Patients who received  $> 75\%$  RDI for Regorafenib AND Avelumab over cycle 1,
- Patients who received  $\leq 75\%$  RDI for Regorafenib OR  $\leq 75\%$  RDI for Avelumab over cycle 1 due to any drug-related AE.

#### Rules of decision for patient's replacement:

- Patients who goes off treatment for toxicity (DLT or any other AE):
  - If RDI  $\leq 75\%$ : Patients will not be replaced. Patients will be considered as having experienced a DLT over the first cycle.
  - If RDI  $> 75\%$ : Patients will not be replaced. DLT status will follow protocol's definition (section 9.1)
- Patients who goes off treatment for reasons unrelated to toxicity (DLT or any other AE), e.g. progression, lost to follow-up, will be replaced.

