## 3.2. PHASE I – DOSE ESCALATION PART

### 3.2.1. Definitions

**Dose-limiting toxicity (DLT)** is defined as an adverse event or laboratory abnormality that fulfills all the criteria below:

- Begins on the first 28 days of treatment
- Is considered to be at least possibly related to the study treatment
- Meets one of the criteria below:
  - Hematotoxicity:
    - Persistent grade 4 neutropenia lasting  $\geq 7$  days;
    - When a neutrophil count of  $< 1000/\text{mm}^3$  and fever of  $\geq 38.0^\circ\text{C}$  is observed for  $> 2$  days;
    - Grade 4 thrombopenia or thrombopenia associated with a hemorrhage requiring platelet transfusion.
    - Grade 3 thrombocytopenia with bleeding.
  - Non-hematotoxicity:
    - $\geq$  Grade 3 non-hematotoxicities are considered as DLTs with the following specifications:
    - $\geq$  Grade 3 diarrhea, nausea, vomiting, and loss of appetite for  $\geq 5$  consecutive days (despite supportive therapy);
    - $\geq$  Grade 3 electrolyte imbalance for  $\geq 7$  consecutive days (despite supportive therapy);
    - Grade 3 dermatologic toxicity (Hand foot syndrome reaction and non-life threatening events) for  $\geq 7$  consecutive days;
    - Grade 4 dermatologic toxicity of any duration;
    - ALT/AST increases 5-8 X ULN with concomitant bilirubin increase  $< 2$  X ULN not resolving to  $< 5$  X ULN within 7 days
    - ALT/AST increases 5-8 X ULN with concomitant bilirubin increase  $> 2$  X ULN
    - ALT/AST increases  $> 8$  X ULN regardless of concomitant bilirubin increase
    - Bilirubin increase  $> 3$  X ULN not resolving to baseline within 7 days
    - $\geq$  Grade 3 immune-related adverse events lasting for  $\geq 8$  consecutive days despite steroid therapy.

In addition, the following will be considered as DLT:

- Any other study drug related AE considered significant enough to be qualified as DLT in the opinion of the investigators after discussion with the sponsor
- Any drug-related AE leading to Regorafenib or Avelumab relative dose intensity lower or equal to 75% over the first treatment cycle.

**Maximum tolerated dose (MTD):** is defined as the highest dose at which no more than 1 in 6 of the patients in the cohort experienced a DLT in the first treatment cycle.

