### 3.2.2. Treatment scheme

Regorafenib will be taken orally once daily for three weeks on/one week off, as appropriate for assigned dose level.

Avelumab will be administered intravenously, at fixed doses of 10 mg/kg, every two weeks, starting on Cycle 1 Day 15.

A treatment cycle consists of 4 weeks. Treatment may continue until disease progression or study discontinuation (withdrawal of consent, intercurrent illness, unacceptable adverse event or any other changes unacceptable for further treatment, etc.).

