- Any other study drug related AE considered significant enough to be qualified as DLT in the opinion of the investigators after discussion with the sponsor
- Any drug-related AE leading to Regorafenib or Avelumab relative dose intensity lower or equal to 75% over the first treatment cycle.

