### 11.2. DEFINITION

#### 11.2.1. *Adverse event*

An adverse event is the development of an undesirable medical condition or the deterioration of a pre-existing medical condition following or during exposure to a pharmaceutical product, whether or not considered causally related to the product. An undesirable medical condition can be symptoms (eg, nausea, chest pain), signs (eg, tachycardia, enlarged liver) or the abnormal results of an investigation (eg, laboratory findings, electrocardiogram). In clinical studies, an AE can include an undesirable medical condition occurring at any time, including run-in or washout periods, even if no study treatment has been administered.

The term AE is used to include both serious and non-serious AEs.

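### The phase I replacement rule counts any adverse-event exit with RDI at or below 75% as a DLT, whereas the DLT definition and the assessable population require drug-relatedness, and it does not say how a DLT before a non-toxicity exit is counted

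*Protocol*

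**What the plan says.** Three parts of the Protocol decide how a phase I patient is scored.

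- **DLT definition (sections 3.2.1 and 9.1.1).** An event must meet all of the listed criteria, one of which is: "Is considered to be at least possibly related to the study treatment". A further criterion based on RDI is also tied to the drugs: "Any drug-related AE leading to Regorafenib or Avelumab relative dose intensity lower or equal to 75% over the first treatment cycle".
- **Population for the primary analysis (section 10.2.1).** A patient is assessable if cycle 1 RDI exceeds 75% for both drugs. A patient at or below 75% for either drug is assessable only on a condition, worded for avelumab as "RDI for Avelumab over cycle 1 due to any drug-related AE". Section 10.3.2.1 analyses the primary endpoint in this population.
- **Replacement rule (also section 10.2.1).** One branch covers "Patients who goes off treatment for toxicity (DLT or any other AE". If RDI is at or below 75%, the patient is not replaced and "Patients will be considered as having experienced a DLT over the first cycle". If RDI is above 75%, DLT status is referred back to section 9.1. The other branch reads: "Patients who goes off treatment for reasons unrelated to toxicity (DLT or any other AE), e.g. progression, lost to follow-up, will be replaced".

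Two further statements bear on the reading. Section 11.2.1 defines an adverse event "whether or not considered causally related to the product". Section 3.2.2 gives avelumab "every two weeks, starting on Cycle 1 Day 15", so one dose is planned in cycle 1.

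**The concern.** The DLT count is the phase I primary endpoint. It determines the maximum administered dose (MAD) and the maximum tolerated dose (MTD), and it informs the RP2D used in every phase II cohort except A'. With three to six patients per level and a limit of one DLT in six, a rule that scores one patient in different ways can matter.

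The replacement rule departs from the definition at one specific point. Above 75% RDI it defers to section 9.1. At or below 75% it assigns DLT status itself, without asking whether the event was related to the drugs.

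Its second branch has a separate gap. It replaces anyone who leaves for a reason other than toxicity and is silent on a DLT already recorded in that patient.

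**Working it through.** The Protocol states no figure that depends on these rules, so there is none to reproduce. The check is a case comparison, followed by an illustration of scale.

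**How easily the threshold is crossed.** The replacement rule does not name the drug whose RDI is meant; I read it as either drug, as in the assessable-population clause.
- Regorafenib, 21 planned days: 15/21 = 71.4% (at or below 75%); 16/21 = 76.2% (above).
- Avelumab, one planned dose on Day 15: leaving before Day 15 gives 0/1 = 0%.

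Any exit before Day 15 therefore falls in the lower branch.

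**Case 1: exit in cycle 1 for an AE judged unrelated, RDI at or below 75%.**

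| Text applied | Status |
|---|---|
| Sections 3.2.1 and 9.1.1 | Not a DLT |
| Section 10.2.1, assessable population | Not assessable |
| Section 10.2.1, replacement rule | DLT, not replaced |

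**Case 2: DLT criterion met, then exit for progression.**
- RDI above 75%, or at or below 75% because of a drug-related AE: a DLT by definition and assessable, yet replaced. How the DLT is counted is not stated.
- RDI at or below 75% because of progression: a DLT by definition, but outside the assessable population and so, through section 10.3.2.1, outside the primary analysis. This can arise because some criteria in section 3.2.1 need no minimum duration, for example transaminases above 8 times ULN or grade 4 dermatologic toxicity.

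**Illustration of over-counting (Case 1).** Let p be the true drug-related DLT rate, u the rate of cycle 1 exits for unrelated AEs, and q the rate counted as DLT:

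q = 1 − (1 − p)(1 − u)

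Under the escalation table in section 3.2.3, a level passes with 0/3, or with 1/3 followed by 0/3:

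P(pass) = (1 − q)³ + 3q(1 − q)⁵, and P(MAD) = 1 − P(pass)

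Worked example, p = 0.15:
- u = 0: q = 0.15; P(pass) = 0.6141 + 0.1997 = 0.814; P(MAD) = 18.6%.
- u = 0.05: q = 1 − 0.85 × 0.95 = 0.1925; P(MAD) = 27.5%.
- u = 0.10: q = 1 − 0.85 × 0.90 = 0.235; P(MAD) = 36.8%.

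| p | P(MAD), u = 0 | u = 5% | u = 10% |
|---|---|---|---|
| 10% | 9.4% | 17.6% | 27.0% |
| 15% | 18.6% | 27.5% | 36.8% |
| 20% | 29.1% | 37.8% | 46.4% |
| 30% | 50.6% | 57.5% | 64.0% |

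**Illustration of under-counting (Case 2).** If a share f of DLT patients were replaced and not counted, q = p(1 − f)/(1 − pf). At p = 30%, P(pass) rises from 0.494 (f = 0) to 0.539 (f = 10%) and 0.642 (f = 30%).

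The values of p, u and f are assumptions; the Protocol gives none of them.

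**The case against.** **The word toxicity may imply drug-relatedness.** If so, Case 1 disappears. But the rule's own gloss extends to any other AE, and section 11.2.1 defines AE regardless of causality. The literal text does not carry the restriction.

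**Counting every AE-driven stop may be deliberately conservative.** It may, and nothing in the Protocol says otherwise. The conflict with the definition and with the assessable population would still need to be resolved.

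**A reader might infer that the rule discards recorded DLTs.** No sentence does. The rule says replaced, which is not the same as removed from the count, and the assessable population keeps most such patients. A DLT leaves the primary analysis only when RDI is at or below 75% for a reason other than a drug-related AE. That gap is narrow, since Appendices 7 and 8 interrupt regorafenib for many grade 3 or 4 toxicities, so low RDI would often be attributable to the DLT.

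**A reader might infer that over-counting distorted the phase II dose.** Section 7.3 gives the phase II regorafenib dose defined by phase I as 160 mg, the highest level allowed in section 3.2.3. Escalation was not held below the top level, so false MAD declarations of the kind tabulated did not lower the dose.

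**The steering committee is a safeguard.** Sections 3.2.3 and 12.1.1 refer questions of DLT status to it, and its oncologists may not comment on patients they treated. This makes mechanical misclassification less likely, but it does not tell the committee which rule to apply.

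**One reclassified patient does not always matter.** Moving from 0/3 to 1/3 only expands the level, and 0/6 to 1/6 changes nothing. The verdict turns only on the step from one to two DLTs. This stands.

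**Conclusion.** The conflict is real and can be read directly from the text. For a patient who stops in cycle 1 because of an unrelated AE with RDI at or below 75%, the Protocol gives three incompatible statuses. The assessable-population clause defines who is analysed, not what a DLT is, so part of the conflict lies inside section 10.2.1 itself.

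The second limb is an omission. The Protocol does not say how a DLT is counted when the patient later leaves for another reason, and in one narrow configuration that patient falls outside the primary analysis population.

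The size cannot be established from the documents. The 3+3 probabilities show the direction and possible scale under assumed rates; they do not describe what happened in phase I. With the phase II dose already set at the top level, what remains at stake is the accuracy of the reported DLT table and a clear rule behind it. None of this shows that any phase I patient was in fact misclassified.

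**What to change.** Reconcile sections 3.2.1, 9.1.1 and both parts of 10.2.1:

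1. Apply one relatedness condition in the DLT definition, the assessable population and the replacement rule. If every AE-driven stop is meant to count, say so in all of them; if only drug-related ones, carry that condition into the replacement rule.
2. State that a patient who has met a DLT criterion stays in the DLT count and in the primary analysis population, whatever the later reason for leaving.
3. Check the 6 to 12 phase I patients for early exits and report the DLT table under the single rule.

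The cost is a few wording changes and a short listing of cycle 1 exits with reason, relatedness and RDI. If no patient was affected, one sentence in the report closes the point. If one was, the report should show that patient's status under the reconciled rule and whether the level's verdict depends on it.
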